# Web- and Mindfulness-Based Intervention to Prevent Chronic Pain After Cardiac Surgery: Protocol for a Pilot Randomized Controlled Trial

**DOI:** 10.2196/30951

**Published:** 2021-08-30

**Keywords:** postoperative pain, cardiac surgery, chronic pain, web-based, mindfulness, mobile phone

## Abstract

**Background:**

Cardiac surgery is a frequently performed procedure. However, pain after cardiac surgery may become chronic (lasting >3 months) in adults. Once discharged from the hospital, patients are at greater risk of developing chronic postsurgical pain (CPSP) and of prolonged opioid use, as they need to self-manage their pain. Psychological risk and protective factors such as pain-related catastrophic thoughts and pain acceptance determine their ability to cope and their use of opioids, which is crucial for self-management of pain. Studies on mindfulness-based cognitive therapy (MBCT) have multiplied their potential effects on pain acceptance and catastrophic thoughts. However, web-based MBCT for the prevention of CPSP has not yet been examined.

**Objective:**

The aim of this study is to pilot test a 4-week-long web-based MBCT intervention for adults following discharge from the hospital by assessing the acceptability or feasibility of the intervention and examining preliminary effects on pain intensity, pain interference with activities and opioid use, and pain acceptance and catastrophic thoughts in the 6 months following surgery.

**Methods:**

A double-blinded pilot randomized controlled trial will be used to assess a web-based MBCT intervention. Patients will be selected according to the following criteria: age ≥18 years; first-time elective cardiac surgery via a median sternotomy; worst pain in the past week score ≥4/10; ability to understand and complete questionnaires in English; and ability to use an electronic device such as a smartphone, computer, or tablet. After baseline measures, 32 participants will be randomized into two groups: one receiving both the brief, 4-week-long web-based MBCT intervention and usual care (experimental group) and the other receiving only one standardized, web-based educational session with weekly reminders and usual care (attention control group). Peer-reviewed competitive funding was received from Florida State University’s Council on Research & Creativity in January 2021, as well as research ethics approval from Florida State University's institutional review board.

**Results:**

Recruitment began in June 2021. Unfortunately, because of the current COVID-19 pandemic, recruitment is not progressing as expected. Recruitment strategies are constantly monitored and updated according to latest data and restrictions surrounding the pandemic.

**Conclusions:**

This research is significant because it targets the trajectory of CPSP, a leading cause of disability and opioid misuse. This is the first study to assess MBCT for the prevention of CPSP after cardiac surgery in the recovery phase. This approach is innovative because it promotes self-management of pain through the modulation of individual factors. If successful, the intervention could be expanded to numerous populations at risk of chronic pain.

**International Registered Report Identifier (IRRID):**

DERR1-10.2196/30951

## Introduction

### Background

Cardiac surgery is a common life-saving procedure [1] that can lead to several complications during recovery. One of them is persistent postoperative pain (ie, pain developing after surgery and lasting at least 3 months with other causes of pain excluded [2]), and its incidence seems to have increased [3]. Estimates suggest that up to 37% of patients undergoing cardiac surgery have persistent pain and will potentially develop chronic postsurgical pain (CPSP; ie, pain lasting for more than 3 months following surgery), with 50% of them reporting moderate to severe postoperative pain [3] that compromises their recovery and daily functioning [3-6]. Furthermore, 10% of the patients will develop new prolonged opioid use (ie, opioid use for more than 3 months) [7], which portends addiction and overdose death [8]. Both chronic pain and chronic opioid use can exacerbate heart disease [9-14]. Compounding this human cost, CPSP is expensive, incurring annual direct and indirect costs of US $41,000 per patient in the United States [15].

Various biopsychosocial factors have been found to increase a cardiac surgery patient’s risk of transitioning from acute pain to CPSP [3,5,16,17]. Modifiable psychosocial factors such as pain catastrophizing (ie, an exaggerated negative mental set brought to bear during actual or anticipated painful experience [18]) and pain acceptance (ie, a person’s engagement to take valuable actions despite the pain [19]) have gained much attention from researchers. Indeed, greater levels of catastrophic thinking are associated with higher perceived pain intensity, and greater levels of pain acceptance are associated with better functioning [20,21]. A behavioral intervention targeting known risk factors during the sensitive, subacute recovery period may prevent CPSP development [16,22,23]. With reduced hospital length of stay after cardiac surgery [24,25], patients are at risk for CPSP and prolonged opioid use [26,27] as they become more isolated with relatively elevated levels of pain after discharge [3,28,29]. Moreover, rarely aware of the risk of CPSP [30], patients may seek pain management support only after their pain has become chronic and disability has already surfaced [31]. Teaching patients undergoing cardiac surgery effective, psychological pain self-management strategies that address common CPSP risk (eg, pain catastrophizing) and protective (eg, pain acceptance) factors is likely to improve their pain coping and decrease their opioid use [26,32-34]. Indeed, pain acceptance and catastrophizing have been shown to be theoretically related and mediate the relationship between pain and clinical outcomes [20,35,36]. The subacute phase following discharge from the hospital may be an optimal time for such an intervention, but there is limited research examining the efficacy of psychological interventions for pain self-management in the subacute phase [34,37]. The evidence comes from rather demanding interventions (eg, 60-minute weekly group sessions for a minimum of 8 weeks with additional homework), whose efficacy may be decreased because of limited patient adherence [34]. Therefore, it is critical to translate knowledge on pain-related psychological risk factors into timely interventions promoting pain self-management in this decisive phase of the postsurgical pain trajectory [23,38-41].

Traditionally, interventions based on cognitive behavioral therapy have been used to treat chronic pain, as considerable evidence suggests that they have a modest effect on pain and may also decrease pain-related disability and depression [42,43]. However, more recently, the number of studies on mindfulness-based interventions (MBIs) for chronic pain has increased tremendously [44-46]. MBIs train patients to engage in self-regulation of attention by increasing their awareness and acceptance of present moment thoughts, feelings, and physical sensations [47]. Some research suggests that MBIs induce adaptive neurobiological changes and that people who practice mindfulness have better pain tolerance (ie, “the maximum intensity of a pain-producing stimulus that a subject is willing to accept in a given situation” [48]) than those who do not [49]. The first wave of MBIs for chronic pain, such as mindfulness-based stress reduction, mindfulness-based cognitive therapy (MBCT), or mindfulness-oriented recovery enhancement, largely consist of eight weekly, 2-hour group therapy sessions [21]. However, more recent MBIs for acute and chronic pain have adopted briefer formats, and preliminary evidence suggests that they may be efficacious as well [50,51]. Although more research is needed regarding their feasibility and efficacy across different settings, brief MBIs have already been shown to (1) decrease hospitalized patients’ pain intensity, pain unpleasantness, and anxiety [52]; (2) decrease surgical patients’ preoperative pain intensity, pain unpleasantness, pain medication desire, and anxiety, as well as improve their physical functioning 6 weeks after surgery [53]; and (3) decrease pain intensity, pain unpleasantness, and opioid use in the first month after surgery [54]. In addition, the benefits of MBIs appear to extend beyond pain. MBIs have also been found to improve stress, depressed mood, and sleep quality [55-57], which are all intertwined with chronic pain. Moreover, MBIs are emerging as promising approaches for mitigating heart disease and promoting cardiac rehabilitation [58-60]. Specifically, MBCT—which combines mindfulness strategies and cognitive therapy—is one of the most widely researched MBIs and may be uniquely suited for pain management given its potential effect on pain-related psychological factors such as catastrophic thinking and pain acceptance [21,61-65].

Our preliminary work with a web- and cognitive behavioral therapy–based intervention in the acute or hospitalization phase after cardiac surgery showed that (1) a brief targeted intervention may be able to modulate modifiable psychological risk factors and reduce postoperative pain interference with activities [66,67], (2) patients express the need for additional pain management support after hospital discharge [39], and (3) clinicians recommend interventions that enhance patients’ engagement in their recovery [38]. However, offering additional support and engaging patients in their care can be challenging in terms of time and resources for clinicians and in terms of accessibility for patients. Nevertheless, eHealth approaches seem promising and have the potential to increase active involvement in one’s health [68]. Moreover, they seem to lead to similar or improved perioperative clinical outcomes compared with face-to-face interventions [69]. To our knowledge [70], our intervention is the only web-based intervention designed to prevent CPSP in patients undergoing cardiac surgery. Furthermore, brief web-based MBCT for pain management or prevention of CPSP has not been examined.

### Objectives

In this study, we will pilot test and evaluate a brief 4-week web-based MBCT intervention designed to promote postoperative pain self-management in patients undergoing cardiac surgery during the subacute phase. Guided by a biopsychosocial framework of pain, our team will accomplish two aims using a pilot randomized controlled trial (RCT) in this stage 1 study [71]: (1) to assess the acceptability and feasibility of the brief web-based MBCT intervention for pain self-management in the subacute phase and (2) to examine the preliminary effects of brief web-based MBCT intervention on pain intensity, pain-related interference with physical and emotional function and opioid use (ie, clinical outcomes), and pain-related catastrophic thinking and pain acceptance (ie, therapeutic mechanisms).

## Methods

### Theoretical Framework

The biopsychosocial model of chronic pain is the framework of this intervention and study, as it is the most comprehensive foundation for understanding, preventing, and treating chronic pain [72,73]. Psychological risk and protective factors are the cornerstone of this model [72,74-76], as they are relatively modifiable factors involved in pain processes and determine individualized pain reactions, including pain self-management behaviors [77]. Among these factors, pain acceptance and pain-related catastrophic thoughts have been recognized for their contribution to CPSP [34] and have been identified as potential contributing factors to the therapeutic mechanism of MBCT [21,61,62]. For these reasons, these two variables are the targets of the intervention (Figure 1).

**Figure 1 figure1:**
[figure not shown]
Conceptual model based on the biopsychosocial model of chronic pain.

### Study Design

A double-blinded pilot RCT will be used to assess the brief web-based MBCT intervention in the 6 months following cardiac surgery (coronary artery bypass grafting and valve replacement). This study received ethical approval from the institutional review board of Florida State University in January 2021. An experienced research assistant (RA) will be responsible for participants’ recruitment and informed consent procedures at the time of follow-up with the surgeon (usually 2-4 weeks after surgery). The study will be advertised in the surgeon’s offices and surgical units with posters and flyers. Social media platforms and newspapers will also be used. If interested, potential participants will contact the RA via telephone or email, and the inclusion criteria will be assessed. After baseline measures have been collected, participants will be randomized into two groups by the principal investigator (PI): one receiving both the brief 4-week web-based MBCT intervention and the usual care procedure (experimental group [EG]); the second group receiving only one standardized educational web-based session in the first week along with weekly reminders for 3 weeks and the usual care procedure (attention control group [ACG]). At the end of the intervention, participants will be asked if they received the intervention to evaluate their blinding. Participants from the ACG will be given the opportunity to receive the entire intervention once the study is complete.

Computer software will generate the randomization schedule: permuted block randomization with block sizes of 4 and an allocation ratio of 1:1. The randomization list and opaque sealed envelopes numbered sequentially will be prepared by the PI’s colleague who will not be involved in this study. The RA who will be responsible for the entire data collection will be blinded to the patient group assignment. Participants in both groups will receive gift cards of US $25 at each of the four data collection time points (baseline, after intervention, 3 months after surgery, and 6 months after surgery) for a total of US $100.

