### Choice of Comparators

Most MBI studies include the usual care control groups. A meta-analysis conducted by the Agency for Health Care Research and Quality including 18,753 articles found that only 47 (3%) trials included an active control treatment [80]. This approach only contributes to showing the absolute benefit of an MBI and fails to demonstrate if that MBI has more value than clinical attention alone. Based on our previous findings, accounting for therapeutic contact with clinicians is important in this phase [38]. Moreover, guidance from clinicians embedded in web-based interventions has an impact on outcomes [81]. Hence, attention control is relevant in highlighting the benefits of MBI. Moreover, ACGs may help mitigate the lack of oversight on usual care by standardizing the information received by people in the control groups [82]. Finally, although it is admitted that double blinding is complex to implement in studies with psychosocial interventions, ACGs may contribute to blinding to a certain extent [82]. Thus, an attention control approach is used in this study. Although the web-based standardized session needs to be credible and includes a video recording from a clinician, it was carefully developed so that it does not include any active ingredient [82,83].

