The intervention will start upon follow-up with the cardiac surgeon (usually approximately 2-4 weeks after surgery). This time frame will allow participants to recover from surgery, return to their routine at home, and experience the challenges of managing persistent pain in their home and daily activities. The intervention will end approximately 6-8 weeks after surgery but before pain is considered chronic (ie, 3 months postsurgery). At the time of enrollment, participants will receive education via telephone and email on how to access and implement the brief web-based MBCT intervention or the attention control intervention. Participants will be informed that weblinks (Qualtrics) for each weekly session will be sent via SMS text messaging or email. The link will redirect participants to a Qualtrics page where video and audio recordings are posted. Qualtrics allows viewing videos from any type of device, for example, a computer, tablet, or smartphone. Participants’ progress and adherence will be monitored on web using Qualtrics.

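### The single end-of-treatment blinding question is ambiguous for control participants and asked late, so an apparently successful blind would be weak evidence

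*Protocol article*

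**What the plan says.** Study Design in the protocol article labels the trial: "A double-blinded pilot RCT will be used to assess the brief web-based MBCT intervention". The same section gives the only check of participant blinding in the article: "At the end of the intervention, participants will be asked if they received the intervention to evaluate their blinding". It also names the other blinded party: "The RA who will be responsible for the entire data collection will be blinded to the patient group assignment".

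Treatment Conditions, in the text after the session outline, says that at enrollment participants are taught "how to access and implement the brief web-based MBCT intervention or the attention control intervention". Both arms' material is therefore called an intervention there. In Study Design, however, the word is used for the mindfulness programme alone: "Participants from the ACG will be given the opportunity to receive the entire intervention once the study is complete".

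Choice of Comparators sets a requirement for the control ("Although the web-based standardized session needs to be credible and includes a video recording from a clinician") and limits what it can achieve: "ACGs may contribute to blinding to a certain extent".

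Data Collection states that measures are taken by telephone interview with entry into Qualtrics. The listed measures cover pain, interference, opioid use, mindfulness, acceptance, catastrophizing and mood. None rates expected benefit or the credibility of the assigned programme.

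**The concern.** Pain intensity, interference and the psychological scales are all rated by the participants. Blinding the data collector does not stop a participant's own expectations from shaping those ratings, so the participant's belief about allocation is the one that matters most. The two programmes differ in content and length: four mindfulness sessions with regular home practice, against one 15-minute education session with three reminders. The article itself expects an attention control to give only partial masking. The check therefore has real work to do.

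Three features weaken it as described. First, a yes from the control arm has two meanings. Second, the question comes only after four weeks, when a guess mixes knowledge of content with how the participant's pain has changed. Third, the control's credibility is required but not measured.

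There is also a practical risk. If the assistant who collects all outcomes asks the question in the telephone interview, the reply could disclose the arm before the 3- and 6-month assessments.

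At stake is what this pilot can tell a later efficacy trial about its comparator, and how much weight the double-blinded label can bear.

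**Working it through.** The article states no figure for the blinding check, so there is none to reproduce. The argument rests on wording; the arithmetic below is an illustration.

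**1. Passages side by side.** Study Design asks whether participants received the intervention. Treatment Conditions uses that noun for both arms; the sentence in Study Design about the later offer to controls uses it for mindfulness only. Two readings are open to a control participant:
- *Literal:* the programme I was given. The truthful answer is yes, whatever the participant believes about allocation.
- *Specific:* the mindfulness programme. The answer is yes only if the participant believes that is what they had.

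**2. Effect on the control arm's yes rate.** Let q be the share of controls who read the question literally, and g the share of the remainder who believe they had the mindfulness programme. The documents give neither; both are assumed and varied from 0 to 1.

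Yes rate: y = q + (1 − q) × g. A conventional arm-level index for controls is 1 − 2y, where 1 means all guess correctly and 0 looks like chance. The protocol states no index; this one is used only to show the effect.

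Suppose every control knows they did not have mindfulness training (g = 0):

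| q | y = q + (1 − q) × 0 | 1 − 2y |
|---|---|---|
| 0 | 0% | 1.0 (unblinding detected) |
| 0.25 | 25% | 0.5 |
| 0.50 | 50% | 0.0 (looks like chance) |
| 1 | 100% | −1.0 |

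**3. Same data, different truths.** A yes rate of 50% arises from q = 0, g = 0.5 (0 + 1 × 0.5) and from q = 0.5, g = 0 (0.5 + 0.5 × 0). A yes rate of 100% arises from q = 0, g = 1 and from q = 1, g = 0. At either value the question cannot separate a masked control arm from a fully unmasked one.

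**4. Where the question still works.** Rearranged, g = (y − q) / (1 − q), which is never larger than y. If y = 0, then g = 0. If y = 25%, g lies between 0 and 25%. A low yes rate among controls therefore shows unblinding on either reading. The ambiguity affects only moderate and high yes rates, which are the results that would look like success.

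**5. Precision.** The planned size is 16 per arm. Exact (Clopper-Pearson) 95% CI for 8/16: 24.7% to 75.3%. On the index scale that is 1 − 2 × 0.753 = −0.51 to 1 − 2 × 0.247 = 0.51. With the article's 20% attrition, 16 × 0.8 = 12.8 remain per arm; at 12, 6/12 has an exact 95% CI of 21.1% to 78.9%. Even an unambiguous question is imprecise at this size.

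**6. Timing.** The control session falls in the first week, so after the first session both arms have had one web session. By the end of the intervention the experimental arm has been offered four. A guess taken only then comes after the programmes have diverged and after any change in pain has been felt.

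**The case against.** The case on the other side is substantial.

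- The sentence reports the question indirectly. The item put to participants and its response options are not shown, and a journal article commonly leaves these to the full protocol. This stands: the criticism applies to the check as described, not to an instrument that has been seen.
- In Study Design the word mainly means the mindfulness programme, and nothing shows that participants meet the phrase used for the control in Treatment Conditions. If no control reads the question literally (q = 0), answers by arm are informative. This also stands, and a clear split would be informative on any reading.
- No scoring rule, index or success criterion is stated. A reader might infer that a control who says yes will be counted as successfully blinded, or that the answers cannot support the blinding claim at all. The article supports neither inference.
- A reader might also infer that the arms are visibly different to participants and the label is therefore false. Each participant sees only their own material, the article does not say what they are told about the other arm, and consent pages are not available. The label also covers the data collector, and Choice of Comparators qualifies it.
- An end-of-treatment check is not an error, and the article treats its effect analyses as illustrative. This limits the seriousness of the point.

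What survives is narrower. The content, timing and purpose of the check are stated choices; as stated, a control yes is ambiguous and the guess is mixed with perceived benefit. The acceptability ratings do not fill the gap: they are taken at the end of the intervention, and the article does not make clear that controls complete them.

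**Conclusion.** The point holds in a limited form. As described, the check can reveal a failed blind but gives only weak support for a successful one. No estimate, sample size or decision rule changes.

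The size of the ambiguity depends on q, which is unknown. At q = 0 it disappears; at q = 0.5, a control arm in which nobody believes they had mindfulness training would look like chance guessing. These values are assumptions, and the index is not the protocol's own.

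The risk to the assistant's blind is conditional: the article does not say who asks the question, only that measures are taken by telephone and that the assistant is responsible for all data collection.

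This is a worthwhile, inexpensive improvement to a stated method. It does not show that the double-blinded label is wrong.

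**What to change.** Replace the question with a self-completed Qualtrics item given to both arms and not visible to the research assistant. It should ask whether the participant believes they are in the programme being tested, the comparison programme, or does not know. Ask it after the first session and again at T1.

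Add a brief expected-benefit or credibility rating after the first session. Report the guesses and ratings by arm, with confidence intervals, beside the effect estimates. Limit the claim about participant blinding to what these data support.

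The cost is a few items on a platform already in use and a change of wording. The downsides are a little participant burden, a blinding claim that may become less favourable, and wide intervals at about 16 per arm. The change will not by itself secure the assistant's blind, because the same assistant is also to conduct the T1 acceptability interviews; that arrangement needs separate attention.
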